### 2.8. Risk Stratification and Intervention Assignment

After the baseline assessment, the multidisciplinary team will identify the clinically relevant and modifiable risks and assign one or more of five intervention domains: urinary, mobility/physical, psychological/cognitive, caregiver, and environmental. Each assignment requires a documented corresponding risk that materially contributes to toileting exposure, unsafe transfer or mobility, or fall risk; is potentially modifiable within the program; and has no clinical contraindication to the proposed intervention.

The domain-level assignment criteria will be standardized across centers, and assignment to one domain will not preclude simultaneous intervention in others. The specific modality, intensity, frequency, duration, and combinations may be tailored to symptom severity, functional capacity, safety, participant goals and preferences, caregiver capacity, and local resources. The planned intervention parameters and subsequent major modifications will be documented prospectively.

Urinary care will target symptoms that drive urgent, frequent, or nighttime toileting; rehabilitation will target deficits in strength, transfer, gait, balance, endurance, or mobility aid use; psychological/cognitive care will target factors that impair safe toileting or adherence; caregiver interventions will address assistance, supervision, or knowledge gaps; and environmental interventions will target modifiable hazards such as lighting, route obstacles, slippery surfaces, handrails, toilet height, and bedside facilities.

The CRF will document the identified risk factor, assigned intervention domain, selected component, clinical rationale, and subsequent modifications. When a potentially indicated component is not delivered because of contraindication, participant preference, caregiver limitation, or resource constraint, the reason will also be recorded. This documentation will support assessment of intervention exposure and risk–intervention concordance.

### 2.9. Intervention Components

To support reproducibility while retaining clinical individualization, each care plan will prospectively specify the intervention component; provider; setting; planned frequency; session duration or daily target when relevant; intended period; initial intensity or assistance; and criteria for progression, reduction, modification, or discontinuation. Actual exposure, adherence, major changes, and reasons for non-delivery or discontinuation will be recorded. The protocol standardizes this minimum specification rather than imposing one dose on a heterogeneous population, consistent with TIDieR principles (Table 4) [26].

#### 2.9.1. Urinary Symptoms and Nocturia Management

Urinary management may include fluid/voiding education, bladder training, scheduled voiding, medication review and optimization, and, when indicated, neuromodulation or electrical stimulation, with the aim of reducing unsafe toileting exposure.

#### 2.9.2. Gait, Balance, and Physical Rehabilitation

Rehabilitation may include strength, balance, gait, transfer, endurance, and targeted exercises plus adaptation of walking aids or wheelchairs. Exercise is a core fall prevention component [11,12].

#### 2.9.3. Psychological and Cognitive Support

Psychological/cognitive care may include psychological support, behavioral strategies, cognitive training, and reminders tailored to cognition, psychological status, function, and social support.

#### 2.9.4. Caregiver Support and Assisted Toileting

Caregiver interventions may include education, safe transfer and toileting instruction, reminders, assisted or scheduled toileting, and supervision during high-risk periods, tailored to dependency, cognition, toileting pattern, and caregiver capacity.

#### 2.9.5. Environmental and Toileting Safety Modification

Environmental care will match identified hazards with measures, such as improved lighting, obstacle or slip reduction, handrails/grab bars, toilet height adjustment, bedside toileting devices, or safer bed-to-toilet routes [13].

### 2.10. Training, Intervention Standardization, Fidelity Assessment, and Quality Assurance

Before implementation, the relevant staff will receive standardized training on eligibility assessment, multidimensional evaluation, risk stratification, intervention assignment and principles, device use when applicable, data collection, confidentiality, and safety reporting. Common manuals, CRFs, and intervention assignment checklists will be used across centers, and training completion will be documented for the personnel involved in assessment or intervention delivery.

Participant-level fidelity will assess completion of protocol-required and clinically applicable baseline assessments; documentation of identified risks and assigned domains; concordance between risks and assigned interventions; initiation of planned interventions or a documented reason for non-delivery; major modifications and their reasons; and completion of required follow-up and safety documentation. Concordance will quantify both whether assigned domains are supported by documented baseline risks and whether clinically relevant risks receive an intervention or a documented reason for non-delivery.

Center-level implementation consistency will be evaluated using assessment completion, risk–intervention concordance, intervention delivery and documentation, adherence to monthly fall surveillance, follow-up completion, data completeness, and protocol deviations. Indicators will be summarized separately for each center and, where informative, by center type.

The coordinating center will review these indicators periodically. Recurrent deficiencies will trigger clarification, targeted retraining, and corrective feedback while preserving the common core protocol and documentation standards.

Fidelity deviations will include unjustified omission of required assessment, intervention assignment without documented indication, omission of indicated intervention without explanation, or failure to document a major care plan modification.

Quality control will cover process fidelity, data quality, and safety through standardized CRFs, range/logic and missing data checks, staff competency and equipment checks, adverse event documentation, and escalation procedures.

### 2.11. Follow-Up, Fall Ascertainment, and Dynamic Adjustment

Participants will be followed for 6 months using a standardized fall surveillance schedule across all centers, with structured contacts at Months 1, 2, 3, 4, and 5 and a final assessment at Month 6. Contacts may be conducted in person, by telephone, or by video according to accessibility; however, the surveillance interval, core questions, fall definitions, and event documentation procedures will be identical across centers. Additional clinical contacts may occur according to need but will not replace the scheduled surveillance.

The 6-month period was selected a priori to balance clinically meaningful prospective observation with feasibility in a multicenter implementation study. It permits estimation of 6-month toileting-related fall occurrence together with short-term changes in urinary symptoms, nocturia, mobility, functional independence, fidelity, safety, and follow-up performance. The monthly structured surveillance is intended to reduce recall-related underreporting; the study is not designed to establish long-term preventive effectiveness, recurrent fall risk beyond follow-up, or long-term organizational sustainability.

At enrollment, participants and/or caregivers will be instructed to record and promptly report any fall during follow-up. At each monthly contact, investigators will use a standardized surveillance form to determine whether a fall occurred since the previous contact and will document the date; relationship to going to, using, transferring on or off, or returning from the toilet; nighttime occurrence; location and circumstances; resulting injury; and assistance available at the time.

A fall is an event in which a participant unintentionally comes to rest on the ground, floor, or another lower level. Toileting-related falls will use the prespecified primary outcome definition. Caregivers may assist in reporting when participants cannot report reliably. Events reported between scheduled contacts will be reconciled at the next contact to avoid duplication.

Missed monthly contacts will be completed as soon as feasible and documented. At Month 6, all fall records will undergo a final completeness and classification review.

Care plans may be modified for new risks, symptom change, poor adherence, adverse events, or changes in function or care environment; major modifications and reasons will be documented.

### 2.12. Outcome Measures

#### 2.12.1. Primary Outcome

The primary outcome will be the 6-month cumulative incidence of at least one toileting-related fall, defined as a fall while going to, using, transferring on/off, or returning from the toilet. It will be calculated as the proportion of participants with ≥1 such fall among those with an evaluable 6-month outcome status and interpreted as event occurrence rather than causal effectiveness (Table 5).

#### 2.12.2. Secondary Outcomes

Number of nighttime toileting-related falls up to 6 months.Total number of falls from any cause up to 6 months.Change in OABSS from baseline to Month 6 among participants with applicable evaluable paired measurements [20].Change in average nocturia episodes per night from baseline to Month 6 using participant/caregiver voiding records.Change in POMA score from baseline to Month 6 among participants eligible for the assessment [21].Change in MBI from baseline to Month 6 [22].

#### 2.12.3. Prespecified RE-AIM Implementation and Safety Outcomes

Reach: Enrollment rate among eligible screened individuals at completion of recruitment.Adoption: Proportion of centers completing initiation requirements and starting enrollment.Adoption: Proportion of designated personnel completing standardized protocol training before study procedures.Implementation: Completion rate of required and clinically applicable baseline assessments.Implementation: Proportion receiving ≥1 documented risk-matched individualized intervention during follow-up.Implementation: Risk–intervention concordance and predefined fidelity deviation frequency during follow-up.Implementation: Completeness of required baseline, intervention, and follow-up data at Month 6.Maintenance: Participant 6-month follow-up completion rate.Maintenance: Proportion of centers continuing protocol-based pathway delivery and follow-up through the 6-month study period.Safety: Proportion experiencing ≥1 adverse event judged as related or possibly related to a study intervention during follow-up.

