## 2. Materials and Methods

### 2.1. Study Design and Setting

This multicenter, prospective, single-arm interventional implementation study will be conducted at 15 Chinese centers representing different levels of healthcare delivery: four tertiary Grade A hospitals, five secondary hospitals, and six primary-level hospitals. Chinese PLA General Hospital is the coordinating center.

The participating centers must have access to the target population; a designated local study team, the capacity to complete standardized multidimensional assessment and longitudinal follow-up; the ability to deliver or coordinate the core intervention domains; and the capacity to comply with common training, case report forms, fall surveillance, data quality, safety reporting, and ethical requirements. These minimum operational requirements are intended to preserve a common implementation standard across settings.

Including different levels of care is intentional and will allow for evaluation under real-world variations in case mix, staffing, rehabilitation capacity, equipment, and service organization. All centers will use the same eligibility criteria, assessment and intervention-assignment framework, outcome definitions, monthly fall surveillance schedule, documentation, training, and safety procedures. Specific intervention modalities may vary with participant-level clinical indications and local resources, but the underlying assessment and decision framework will remain standardized.

All participants will enter the same integrated pathway. There is no concurrent control arm, treatment allocation, or masking because the interventions are assigned based on a prespecified risk assessment and clinical indications.

The pathway comprises screening and consent, standardized baseline assessment; risk stratification; individualized multicomponent care; monitoring; reassessment; and adjustment according to response, adherence, safety, and changing risk. The follow-up will last 6 months (Figure 1; Table 1).

Figure 1 summarizes the screening, baseline assessment, risk stratification, individualized multicomponent intervention, monitoring and adjustment, 6-month outcome assessment, and integrated clinical and RE-AIM evaluation.

The protocol follows relevant prospective study-reporting principles and SPIRIT guidance [15,16].

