### 2.2. Study Objectives

The primary clinical objective is to estimate the 6-month cumulative incidence of at least one toileting-related fall among participants managed through the pathway; this is an estimate of event occurrence, not causal effectiveness.

The secondary clinical objectives are to characterize nighttime and total falls and changes in urinary symptoms, nocturia, mobility, and functional independence. The implementation objectives are to assess the reach, adoption, delivery, fidelity, follow-up, data quality, and safety.

We hypothesize that the standardized pathway can be implemented consistently across levels of care, as assessed by the prespecified RE-AIM and fidelity measures. The clinical outcomes will be exploratory and will not be interpreted as confirmatory evidence of effectiveness.

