Adoption	Uptake of the pathway by participating centers and designated clinical/research personnel	Proportion of participating centers completing study initiation requirements and initiating enrollment; proportion of designated personnel completing standardized protocol training	Center initiation records and training logs; before and during recruitment
Implementation	Extent to which the standardized assessment, intervention assignment, delivery, and documentation procedures are implemented as intended	Completion of clinically applicable baseline assessments; proportion receiving risk-matched intervention; risk–intervention concordance; protocol fidelity/deviation rate; intervention documentation; required data completeness	CRFs, intervention records, fidelity records, and coordinating-center review; baseline through Month 6
Maintenance	Continued participation in and use of the pathway during the prespecified 6-month study period	Participant 6-month follow-up completion rate; proportion of centers continuing protocol-based follow-up and pathway delivery for enrolled participants through completion of the study follow-up period	Follow-up records and center implementation records; Month 6

**Table 3 healthcare-14-02794-t003:** Multidimensional risk assessment, intervention, and outcome matrix.

Risk Domain	Core Assessment	Potential Intervention Components	Prespecified Outcomes
Urinary function	OABSS; urinary frequency; urgency; nocturia; urinary incontinence; voiding difficulty; voiding diary; clinically indicated PVR and Qmax	Behavioral and bladder training; fluid and voiding management; scheduled toileting; clinically indicated medication optimization; neuromodulation or electrical stimulation when appropriate	Toileting-related falls; nighttime toileting-related falls; OABSS; nocturia episodes
Gait, balance, and physical function	Muscle strength and tone; joint mobility; sit-to-stand and transfer ability; gait; balance; Tinetti assessment; mobility aids	Balance and gait training; strength and endurance training; transfer training; assistive device adaptation; rehabilitation therapy	Total falls; Tinetti score; Modified Barthel Index

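### The adoption measures describe start-up among centers preselected for capacity and completion of training already planned for staff, not center- and staff-level uptake

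*Protocol article*

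**What the plan says.** Section 2.3 describes the adoption domain of RE-AIM as uptake by centers and staff, and Section 2.2 names adoption among the implementation objectives. The outcome list in Section 2.12.3 gives the center measure as "Adoption: Proportion of centers completing initiation requirements and starting enrollment". Table 2 states the denominator: "Proportion of participating centers completing study initiation requirements and initiating enrollment". Table 5 uses the same denominator.

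Section 2.1 sets the conditions for being a participating center: "The participating centers must have access to the target population; a designated local study team", then capacity for assessment and follow-up, "the ability to deliver or coordinate the core intervention domains; and the capacity to comply with common training". The compliance condition reads in full: "the capacity to comply with common training, case report forms, fall surveillance, data quality, safety reporting, and ethical requirements". The 15 centers are "four tertiary Grade A hospitals, five secondary hospitals, and six primary-level hospitals", and Sections 2.6 and 2.18 plan enrollment at all 15 between 1 September and 31 December 2026.

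The staff measure in Section 2.12.3 and Table 5 is the share of designated personnel who complete protocol training before they take part in study work. Section 2.10 schedules that training: "Before implementation, the relevant staff will receive standardized training".

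The article gives no adoption target or threshold. The limitations in Section 4 do not mention that centers are selected on capacity.

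**The concern.** A measure of uptake needs a denominator of units that could have taken the pathway up, including those that did not. Here the center denominator starts after selection. A center that was approached and declined, or was assessed and found unable to meet a Section 2.1 requirement, is not counted in any adoption measure. Within the selected set, enrolling a single participant is enough to count as having started. The staff measure begins with people already designated and asks whether they completed a step that the protocol itself schedules.

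The protocol's Reach measure shows the contrast. It divides those enrolled by all eligible screened individuals, so people who do not enter count against it. Adoption has no counterpart at center level.

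What is at stake is the interpretation of one RE-AIM domain. An adoption figure near 100% could be reported as evidence that hospitals and staff took the pathway up, when it would mainly show that site selection and start-up worked. Since capacity-based selection is not listed as a limitation, nothing in the article warns against that interpretation.

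**Working it through.** **1. The plan's own precision figures.** Section 2.14 gives maximum 95% half-widths for participant-level proportions. With half-width = 1.96 × √(0.25/n):

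| n evaluable | Computed (points) | Stated (points) |
|---|---|---|
| 300 | 5.66 | 5.7 |
| 270 | 5.96 | 6.0 |
| 255 | 6.14 | 6.1 |
| 240 | 6.33 | 6.3 |

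These reproduce, but they do not apply to center adoption, where n = 15. The article gives no expected value or precision for adoption.

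**2. Center adoption if the plan is followed.** Inputs: 15 participating centers (Section 2.1), all planned to enroll (Section 2.6). The estimate is 15/15 = 100%. When all n units succeed, the exact (Clopper-Pearson) lower limit is 0.025^(1/n), so 0.025^(1/15) = 78.2%. With one non-starter, 14/15 = 93.3% (68.1 to 99.8). With two, 13/15 = 86.7% (59.5 to 98.3).

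**3. By level of care.** With the same formula, full start-up gives:

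| Level | Starting | Exact 95% lower limit |
|---|---|---|
| Tertiary | 4/4 | 39.8% |
| Secondary | 5/5 | 47.8% |
| Primary | 6/6 | 54.1% |

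All three estimates would be 100% with wide intervals, so the measure would say little about differences between levels.

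**4. How firm is the expectation of a figure near 100%?** Let each selected center start with probability p, independently. The values of p are assumptions; the article gives none. The chance that at least 14 of 15 start is 15p¹⁴(1−p) + p¹⁵:

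| p (assumed) | P(at least 14/15) |
|---|---|
| 0.90 | 0.549 |
| 0.95 | 0.829 |
| 0.98 | 0.965 |

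A result of 14/15 or better is likely if selected centers rarely fail to start, but it is not guaranteed.

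**5. What an approached-center denominator could change.** The number approached is not in the document, so this is illustration only, with 15 centers starting in each row.

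| Approached (assumed) | Adoption |
|---|---|
| 15 | 15/15 = 100% |
| 20 | 15/20 = 75% |
| 25 | 15/25 = 60% |
| 30 | 15/30 = 50% |

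The first row shows that the difference may be zero.

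**6. Staff measure.** No count of personnel is given, so no figure can be computed. Set side by side, Section 2.10 plans training for relevant staff before implementation, and the measure asks what share of designated staff had it before study procedures. If the plan is carried out, the answer is near 100%.

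**The case against.** The strongest defense is that the measures are openly scoped and do record something. Tables 2 and 5 say participating centers and designated personnel in so many words. Section 2.1 requires ability and capacity, whereas the measure counts an event: initiation completed and enrollment begun, within a four-month recruitment period. A capable center may still not start. Section 2.10 states no bar on untrained staff working, so an untrained designee would lower the staff figure. The initiation requirements are not itemized, so their overlap with the Section 2.1 conditions is an inference. All of this stands. A reader might infer that adoption must be 100% by construction; the documents support a strong expectation, not a certainty.

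A reader might also infer that the hypothesis that "the standardized pathway can be implemented consistently across levels of care" cannot be supported. That does not follow. Section 2.10 lists the indicators of center-level consistency: assessment completion, concordance, delivery and documentation, surveillance adherence, follow-up completion, data completeness and deviations. Adoption is not among them. Section 2.15 summarizes implementation and fidelity indicators by center type, and Section 2.8 records components not delivered because of resource constraint. Those measures can vary among the selected centers and carry most of the weight for the hypothesis.

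Nor do the documents show that primary-level hospitals were screened out. The condition is to deliver or coordinate the domains, so a center without an in-house service may qualify, and nothing shows that any center declined.

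Finally, site-approach records are often kept in operational files, and their absence from an article is no fault. The point here is different: the denominator is stated, in three places, and does not match the construct that Section 2.3 names.

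**Conclusion.** The point holds for the adoption domain only. As defined, the center measure describes start-up completion among centers already judged capable, and the staff measure describes compliance with a planned training step. If the plan is followed, both are expected near 100% (centers 15/15, exact 95% CI 78.2 to 100), and neither then measures the uptake that Sections 2.2 and 2.3 set out to assess.

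This rests on two assumptions: that centers were in fact admitted under the Section 2.1 conditions, and that the unlisted initiation requirements overlap with them. How far reported adoption would differ from uptake among centers approached cannot be determined from the article, and the difference may be nil. The primary outcome, the secondary outcomes and the remaining RE-AIM measures are untouched.

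**What to change.** - In Section 2.12.3, Table 2 and Table 5, report center adoption as centers starting enrollment divided by centers approached or assessed for participation, by level of care. For each center that did not join, give the unmet Section 2.1 requirement or the reason for declining.
- Keep the present figures under accurate labels: *site activation* for centers and *training compliance* for staff. No wider staff denominator is proposed, because the article offers no workable definition of all staff who could have taken part.
- Add to the limitations in Section 4 that conclusions on adoption and implementability apply only to centers meeting the Section 2.1 requirements.

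If the approach records cannot be reconstructed, the relabeling and the limitation are enough to prevent the misreading.

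The cost is a site-selection log from the coordinating center, partly compiled in retrospect, and some wording. The adoption figure may come out less favorable. Section 2.18 states that recruitment had not begun as of 1 August 2026, so the change could be made before any participant is enrolled.

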The RE-AIM and intervention fidelity outcomes will be summarized according to their prespecified operational definitions using frequencies, proportions, and 95% confidence intervals where appropriate, overall and by center. The risk–intervention concordance, fidelity deviations, assessment completion, intervention delivery, data completeness, and follow-up completion will be reported transparently. Intervention exposure will be described by the intervention domains and components received, initiation and delivery, adherence where applicable, and major modifications during follow-up, both overall and, where informative, by center and relevant participant subgroups. Because intervention assignment and intensity will be individualized according to clinical indications, the exposure analyses will remain descriptive and will not be used to infer causal treatment effects.

Enrollment, follow-up completion, and evaluability will be reported separately with reasons for loss and missing data patterns. For the primary outcome, extreme-case sensitivity bounds will alternatively classify participants with incomplete 6-month status and no prior documented toileting-related fall as event positive or event negative. The continuous secondary outcomes will use available paired measurements with missingness reported.

No multiplicity adjustment is planned for exploratory clinical or subgroup analyses. Tests will be two-sided, with an emphasis on effect estimates and 95% confidence intervals.

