Environmental	Lighting; route; handrails; non-slip measures; toilet height/bedside device adaptation	Multidisciplinary team, caregiver, or local service personnel	Required modification(s) and implementation timing	Match identified hazards, safety, and feasibility	Completion/non-completion and reason

**Table 5 healthcare-14-02794-t005:** Prespecified clinical, implementation, and safety outcomes.

Outcome Category	Outcome Measure	Time Frame
Primary	The 6-month cumulative incidence of at least one toileting-related fall	Up to 6 months after enrollment
Secondary	Number of nighttime toileting-related falls	Up to 6 months after enrollment
Secondary	Total number of falls from any cause	Up to 6 months after enrollment
Secondary	Change in OABSS	Baseline and Month 6
Secondary	Change in average nocturia episodes per night	Baseline and Month 6
Secondary	Change in Tinetti Performance-Oriented Mobility Assessment score	Baseline and Month 6
Secondary	Change in Modified Barthel Index	Baseline and Month 6
Reach	Enrollment rate among eligible screened individuals	At completion of recruitment
Adoption	Proportion of participating centers completing study initiation requirements and initiating participant enrollment	During the recruitment period
Adoption	Proportion of designated study personnel completing standardized protocol training	Before participation in study assessment or intervention delivery
Implementation	Completion rate of protocol-required and clinically applicable multidimensional baseline assessments	At baseline
Implementation	Proportion of participants receiving at least one documented individualized intervention matched to identified risk factors and clinical indications	Up to 6 months after enrollment
Implementation	Risk–intervention concordance rate	During the 0–6-month intervention period
Implementation	Proportion of participants with ≥1 predefined intervention fidelity deviation	Up to 6 months after enrollment
Implementation	Completeness of protocol-required study data	At Month 6
Maintenance	Six-month participant follow-up completion rate	At Month 6
Maintenance	Proportion of participating centers continuing protocol-based pathway delivery and follow-up for enrolled participants through completion of the 6-month study period	At completion of the 6-month study follow-up period
Safety	Proportion experiencing intervention-related or possibly related adverse events	Up to 6 months after initiation of intervention

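### The defined delivery outcomes could separate care received from care explained away: receipt is scored at one intervention or more, and concordance accepts a documented reason in place of delivery

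*Protocol article*

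**What the plan says.** Section 2.8 lets the team assign one or more of five intervention domains to a participant. The CRF records the reason when an indicated component is "not delivered because of contraindication, participant preference, caregiver limitation, or resource constraint".

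The prespecified outcomes contain one measure of what participants received. Section 2.12.3 words it as "Proportion receiving ≥1 documented risk-matched individualized intervention during follow-up". Table 5 has the same threshold: "Proportion of participants receiving at least one documented individualized intervention matched to identified risk factors and clinical indications". Table 2 shortens it to "proportion receiving risk-matched intervention".

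Section 2.10 defines concordance in two halves. The first is whether each assigned domain is backed by a documented baseline risk. The second is "whether clinically relevant risks receive an intervention or a documented reason for non-delivery". Table 5 lists the result as a single concordance rate. Among the fidelity deviations in 2.10, the one that bears on delivery is "omission of indicated intervention without explanation".

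Delivery also appears outside the outcome list. Section 2.10 names "risk–intervention concordance, intervention delivery and documentation" among the center-level indicators. Section 2.15 says that "intervention delivery, data completeness, and follow-up completion will be reported transparently", and then plans a description of the domains and components received, with their initiation and delivery, by center where informative. Neither place gives a delivery rate with a numerator and denominator.

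**The concern.** The study's one hypothesis (2.2) is that the pathway can be implemented consistently across levels of care, and it is to be assessed by the prespecified RE-AIM and fidelity measures. The Discussion expects staffing, equipment and rehabilitation capacity to produce differences in delivery between centers, and 2.15 summarizes the indicators by center type to show such variation.

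The defined outcomes are least informative on exactly this. A center short of rehabilitation staff can deliver one component per participant, record resource constraint for the rest, and look the same on the listed outcomes as a center that delivers everything. Contraindication and patient choice are proper reasons not to deliver. Resource constraint is different: it is the capacity limit that an implementation study across tertiary, secondary and primary hospitals should bring out.

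**Working it through.** **The plan's own figures.** The plan gives no delivery figure to reproduce. The half-widths in 2.14 check out: 1.96 × √(0.25/n) gives 5.66, 5.96, 6.14 and 6.33 points for n = 300, 270, 255 and 240, against the stated 5.7, 6.0, 6.1 and 6.3. They concern sampling precision and do not bear on what is counted.

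**What follows from the definitions alone.** Take a participant with k assigned domains (k up to 5, section 2.8), each resting on a documented risk. One domain is delivered, and a reason is recorded for the other k − 1.

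- Receipt outcome (2.12.3, Table 5): met, since one intervention was received.
- Concordance (2.10): met in full. Every assigned domain has a documented risk, and every risk has either an intervention or a reason.
- Omission deviation (2.10): none, since nothing was left unexplained.
- Assigned domains delivered: 1/k, that is 50.0%, 33.3%, 25.0% or 20.0% for k = 2, 3, 4 or 5.

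If every participant had this pattern, the three outcomes would read 100%, 100% and 0%. No rate is assumed.

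**Illustration on assumed values.** Suppose center A delivers each assigned domain with probability p = 0.9 and center B with p = 0.5, independently across domains, with one risk per domain. The true gap is 40 points. None of these values is in the protocol.

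Receipt of at least one = 1 − (1 − p)^k:

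| k | A (%) | B (%) | Gap (points) |
|---|---|---|---|
| 2 | 99.0 | 75.0 | 24.0 |
| 3 | 99.9 | 87.5 | 12.4 |
| 4 | 99.99 | 93.75 | 6.24 |
| 5 | 100.0 | 96.88 | 3.12 |

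Let e be the share of omissions with a recorded reason. The second half of concordance = p + (1 − p)e, so its gap is 40(1 − e) points. Participants with an omission deviation = 1 − [1 − (1 − p)(1 − e)]^k, shown for k = 4:

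| e | Concordance A / B (%) | Gap (points) | Omission deviation A / B (%) |
|---|---|---|---|
| 0 | 90 / 50 | 40 | 34.4 / 93.8 |
| 0.5 | 95 / 75 | 20 | 18.5 / 68.4 |
| 0.8 | 98 / 90 | 8 | 7.8 / 34.4 |
| 1 | 100 / 100 | 0 | 0 / 0 |

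So concordance and the deviation outcome expose the gap only as far as reasons go unrecorded. The better the documentation, the less they say about delivery.

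**At the size of one center.** Equal enrollment, also an assumption, gives 300/15 = 20 participants per center. With k = 4, the receipt outcome would be about 19/20 in B (exact 95% CI 75.1–99.9%) and 20/20 in A (83.2–100%), which overlap almost wholly. Domains delivered would be about 40/80 (38.6–61.4%) against 72/80 (81.2–95.6%), ignoring correlation within participants.

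**The case against.** The strongest reply is that delivery is reported elsewhere. Section 2.15 plans to describe exposure by domain and component received, with initiation and delivery, overall and by center where informative. Section 2.10 names intervention delivery as a center-level indicator beside concordance. Table 4 has a column for exposure and fidelity that, for several domains, keeps non-delivery and its reason apart from delivery. A gap as wide as the one illustrated would probably be judged informative. Concordance is also a fair measure of whether the decision process was followed, and in individualized care a justified omission should not count as failure. Finally, this is a condensed article, and formulas for indicators may stand in the analysis plan.

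Much of this stands. A reader might infer that under-delivery would be concealed, or that a test of the hypothesis is undermined. The documents support neither: the exposure description would show part of it, no formal test or success threshold is set, and the center findings are called descriptive. Nor can a participant score as having received care with nothing delivered, since the receipt outcome requires actual receipt.

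What does not stand is the appeal to missing detail. The threshold of one and the rule that a reason suffices are stated in the article, and an analysis plan consistent with them would inherit both. The exposure description is not among the listed outcomes, and its breakdown by center is conditional.

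**Conclusion.** The point holds as a cheap improvement to the definitions and not as a flaw in the design. The defined receipt, concordance and deviation outcomes can all be perfect while as little as 1/k of assigned domains is delivered, down to 20% when all five are assigned. That floor follows from the text alone. It is a bound on what the outcomes allow and no forecast of what centers will do. The 90% versus 50% comparison rests on assumed delivery rates, assumed documentation shares and independence between domains, and shows only how the measures would behave. The consequence is limited to description: under-delivery would be partly visible in the exposure summaries, but not in the outcomes named for judging consistent implementation.

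**What to change.** In 2.10, 2.12.3 and Table 5:

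- Report the second half of concordance in two parts, intervention received and reason documented but not received. Keep documented clinically relevant risks as the denominator, as 2.10 has it. Tabulate the reasons, with resource constraint separate from contraindication, participant choice and caregiver limits, so that appropriate non-delivery is not held against a center.
- Beside the existing receipt outcome, add the per-participant proportion of assigned domains in which at least one component was delivered.
- Give both by center and by center type.

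Both measures are needed. Section 2.8 allows combinations to be tailored to local resources, so a domain that a center never assigns would drop out of the second measure but not the first.

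The cost is some rewording and one or two more tables. Risks, assigned domains, components, delivery and reasons are already to be recorded (2.8, 2.9, Table 4), and recruitment had not begun on 1 August 2026 (2.18). The downside is that the delivery figures will look less favorable.
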